In keeping with UHCW SOPs, a risk assessment will be implemented, focusing on ensuring safe exercise assessment and prescription for people with AF. Primarily this will involve undertaking appropriate pre-exercise screening; an assessment to ensure the participant can take part in the intervention, both at the Atrium Health Centre, and at their home safely whilst also making sure that they can safely take part in the cardiopulmonary exercise tests. Also, that there will be the provision of appropriately trained staff, suitable facilities, remote supervision, and a comprehensive emergency strategy, with thorough clinical procedures for implementation. Participants will be advised initially to have another adult present at home when carrying out exercises as part of the intervention.

CPET will take place in a UKAS accredited IQIPS standard laboratory. A fully trained member of the research team will run these tests. If a participant is identified to be contraindicated to an exercise test, then their eligibility for the study will be reviewed (i.e., whether the contraindication is temporary in preventing an exercise test).

Physical activity carries a very small risk for patients with AF. Physical activity is likely to cause tiredness, breathlessness, and sore muscles however this is to be expected when starting a new exercise programme and should not be treated as adverse events.

The standard ablation procedure will be carried out by qualified staff members at UHCW. Ablation carries a small risk of further complications which are outlined below:

- <1% risk of vascular injury (including needing surgery)
- 1% risk of pericardial effusion/tamponade
- ~1% risk of stroke
- ~1% risk of phrenic nerve injury
- <1% risk of AV block needing pacing
- 0.5% risk of pulmonary vein stenosis
- Risk of needing emergency cardiac surgery (1:400)
- Other small risks: needing blood transfusion

Any of the above events that occur during the CREED AF study following an AF procedure will be monitored by the trial team and recorded as an adverse outcome of ablation. If it becomes apparent that the CREED AF intervention group are experiencing a statistically significant greater number of these events than the control, then this will be raised and reported in line with local Trust SOPs and reported to the REC as appropriate.

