# **ADVERSE EVENT MANAGEMENT**

- 1. **Adverse Events**

An Adverse Event (AE) is defined as any untoward medical occurrence involving a participant, which does not necessarily have a causal relationship with the intervention or trial.

**Expected** **AEs,** related to the exercise outcome assessments or the exercise intervention, include ‘normal’ levels (for the individual) of:

- Breathlessness
- light headedness/dizziness
- muscle and joint stiffness/soreness
- tiredness/fatigue

There are a few AEs which are expected following AF ablation and occur after roughly 2-4% of all AF ablation cases. These AEs are listed below:

- Vascular injury
- Pericardial effusion/tamponade
- Stroke/Transient Ischaemic Attack
- Myocardial Infarction
- Phrenic nerve injury
- Atrioventricular block
- Pulmonary vein stenosis

Of these conditions there is a small risk (1:400) of requiring further cardiac surgery or a blood transfusion. Each AE will be assessed by the CI or a delegated clinician to assess causality to the CREED AF intervention. In the unlikely event that it is decided that one of the above post AF ablation conditions is related to the CREED AF intervention this will be reported as such in line with local Trust policy and national safety reporting guidelines.

Recording procedures will be the same for both trial groups. Expected AEs will be recorded on the CRF (AE form).

**Unexpected AEs** related to the exercise outcome assessments or the exercise intervention for both the intervention and usual care groups, will be recorded on the appropriate CRF (AE form) and returned routinely to UHCW. Unexpected AEs will be logged and reported at TMG meetings. Should multiple of the same unexpected AE occur during the trial period then this will trigger the TMG to review the study procedures to see if there are any changes that need to be implemented.

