AEs in the intervention group will be determined through patient report at either their in-person intervention session, exercise outcome assessment (CPET) or via their 1-to-1 appointments with the research team (online, in person or over the phone), including a follow-up phone call the day after the outcomes assessment (VO_2peak_) appointments until resolution of the event. AEs in the standard care group will be determined via a check of their medical records, on the day of their exercise outcome session (CPET), and a follow-up phone call the day after the outcomes assessment (VO_2peak_) appointments until resolution of the event.

- 1. **Serious Adverse Events (SAEs)**

Over the study period, people may be admitted to hospital for reasons other than their AF ablation procedure. Admissions data will be collected from self-report and via medical records checks.

For CREED AF, an SAE will be an untoward medical occurrence that fulfils one or more of the following criteria:

- Results in death
- Is life-threatening
- Requires hospitalisation or prolongation of existing hospitalisation
- Results in persistent or significant disability or incapacity
- Requires medical intervention to prevent one of the above, or is otherwise considered medically significant by the investigator

All admissions to hospital are an SAE. The following SAEs are expected with CREED AF and **do not** require additional reporting for this trial, but must be recorded in the relevant section(s) of the CRF:

- Disease progression: worsening symptoms/AF attrition unrelated to the exercise intervention.
- Treatment, which was elective or pre-planned, for a pre-existing condition, not associated with any deterioration in condition.
- General care, not associated with any deterioration in condition.

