**Reportable SAEs - intervention group:** SAEs related to exercise sessions (remote or group sessions within the Atrium Health Centre), or outcomes assessments (VO_2peak_) are possible. In the intervention group, any event that occurs at any time (remote or group sessions within the Atrium Health Centre,) between baseline outcomes assessment and the 10 weeks (±2 weeks) post-AF ablation, or within 24 hours of the outcome assessment appointments (VO_2peak_), will be recorded and reviewed by the chief investigator to determine if it is directly attributable to the intervention, and investigated in line with UHCW’s SOP. This will be determined by participant report at each intervention session or 1-to-1 education session and a follow-up phone call the day after the outcomes assessment (VO_2peak_) appointments until resolution of the event.

If a participant has not attended two consecutive in-person intervention appointments at the Atrium Health Centre, without informing a member of the CREED AF study team, their status will be checked on local electronic clinical records by the local CREED AF clinical rehabilitation team (with participant consent). If their status is unclear, the CREED AF clinical rehabilitation team will attempt to make contact on the phone at least three times.

**Reportable SAEs - standard care group**: any event occurring within 24 hours of each of the assessment appointments (baseline and 10 weeks (±2 weeks) post ablation) will be recorded and reviewed to determine if it is directly attributable to the trial; this will be determined via a phone call to the participant the day following their appointment.

All participants experiencing SAEs during the period up to the 12-month assessments or during the 24-hour periods after the baseline and 10 weeks (±2 weeks) post-AF ablation outcomes assessment (VO_2peak_) will be followed-up until resolution of the event.

The causality of SAEs (i.e. relationship to trial intervention) will be assessed by the investigator(s) using the SAE form (Table 2).

*Table 2: SAE Causal relationship*

| **Relationship**  **to trial intervention** | **Description** |
| --- | --- |
| Unrelated | There is no evidence of any causal relationship |

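### Adverse events are found by different routes in the two arms although recording is said to be the same, and the between-arm escalation rule for ablation complications needs a significant excess that 53 per arm will rarely show

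*Protocol*

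**What the plan says.** **Recording.** The Adverse Events section (protocol section 13) states "Recording procedures will be the same for both trial groups".

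**How AEs are found.** The same section then separates the arms. For the intervention: "AEs in the intervention group will be determined through patient report at either their in-person intervention session", and also at the CPET, at 1-to-1 appointments and through a call the day after the CPET. For controls: "AEs in the standard care group will be determined via a check of their medical records", together with the CPET day and the same next-day call.

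**Reportable SAEs.** In the Serious Adverse Events section the intervention-arm text begins "In the intervention group, any event that occurs at any time". A parenthesis about remote or group sessions follows, then a period from baseline to 10 (±2) weeks post-ablation, or 24 hours around a CPET. For standard care it is "any event occurring within 24 hours of each of the assessment appointments", meaning baseline and 10 weeks.

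**Escalation of ablation complications.** Under Assessment and Management of Risk (section 9), the listed complications are reported onward if the intervention group is found to be "experiencing a statistically significant greater number of these events than the control".

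**Exercise symptoms.** The same part of section 9 says that tiredness, breathlessness and sore muscles "should not be treated as adverse events". Section 13 lists breathlessness, fatigue and muscle soreness as expected AEs and has expected AEs entered on the AE form.

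**The concern.** A reader who sees that recording is the same in both groups will take AE counts by arm as like for like. They are not. One arm is asked repeatedly during training. The other is found mainly through its notes and two assessment visits. A difference in counts could then reflect how events were looked for and not how often they occurred.

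The escalation rule is a separate matter. It is the only place where the protocol turns a between-arm safety count into an action, and the action depends on a significance test in a trial sized for VO2peak. If the test can hardly ever be met at complication rates of a few percent, the rule protects little.

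The two statements on exercise symptoms cannot both be followed. The choice mostly affects the arm that exercises.

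**Working it through.** **1. The routes side by side.**

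| | Intervention | Standard care |
|---|---|---|
| AE sources named | In-person sessions, CPET, 1-to-1 appointments, next-day call | Records check, CPET day, next-day call |
| Records check named for AEs | No | Yes |
| Reportable SAEs | Baseline to 10 (±2) weeks post-ablation, or 24 h around CPET | 24 h around two assessments |
| Admissions; SAEs followed to 12 months; MACE | Not separated by arm | Not separated by arm |

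*Contacts.* The compliance definition uses 12 exercise sessions per phase, so 12 + 12 = 24. Adding 6 education sessions, 2 CPETs and 2 calls gives 34 planned opportunities to report. Controls have 2 CPETs + 2 calls = 4, plus the records check. The figure of 34 is generous for AEs, because only in-person exercise sessions are named there.

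*Reportable-SAE window.* In Table 1 ablation is in week 9, and 8 to 12 weeks later is week 17 to 21. If the intervention window is continuous, that is 17 × 7 = 119 to 21 × 7 = 147 days, against 2 days in controls: 119/2 ≈ 60 to 147/2 ≈ 74 times as long. If the parenthesis limits the clause to events at sessions, this ratio does not apply.

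**2. What unequal capture could do to AE counts.** Assumptions: equal true rates, 53 per arm, two-sided Fisher test at 5%, full capture in the intervention arm and partial capture in controls. The entries are the probability of a false finding of significantly more events in the intervention arm.

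| True rate | Control capture 100% | 50% | 25% |
|---|---|---|---|
| 10% | 0.0095 | 0.070 | 0.180 |
| 20% | 0.015 | 0.214 | 0.547 |
| 30% | 0.015 | 0.379 | 0.816 |

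The capture fractions are illustrative; the protocol gives none. By symmetry, if the intervention arm were the one under-captured (it has no named records check), the same probabilities would apply to a false excess in controls.

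**3. The escalation rule.** The protocol names no test, level or timing. I assumed a two-sided Fisher test at 5%, one look, and all 53 per arm ablated. Section 13 puts ablation complications at roughly 2–4%.

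Smallest significant splits:
- 5 v 0: p = 0.057, not significant; 6 v 0: p = 0.027
- 7 v 1: p = 0.060, not significant; 8 v 1: p = 0.031
- 10 v 2: p = 0.028

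Probability that the rule fires, summing the binomial probabilities of all significant splits with more events in the intervention arm:

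| Control risk | Intervention risk | Expected events (53 × risk) | P(fires) |
|---|---|---|---|
| 3% | 6% | 1.6 v 3.2 | 2.4% |
| 3% | 9% | 1.6 v 4.8 | 11% |
| 4% | 8% | 2.1 v 4.2 | 5% |
| 4% | 12% | 2.1 v 6.4 | 18% |

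**4. Is unequal ascertainment what spoils the rule?** I repeated step 2 at complication rates. The false-signal probability is at most 0.0006 at a 2% rate and at most 0.0154 at 4%, even if controls captured only 10% of events. The rule's weakness is low power, not spurious firing.

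**The case against.** Several points on the other side stand.

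- **No between-arm AE or SAE analysis is planned.** The objectives and the statistics section contain none. The planned safety-type comparison, MACE at 12 months, comes from hospital records in both arms. The harm is to whatever AE table is later shown by arm, not to a stated analysis.
- **The most serious events are partly protected.** All admissions count as SAEs and are collected by self-report and records checks without distinction by arm. SAEs up to 12 months are followed in all participants. Table 1 marks AE reporting at every stage from consent onward with no arm-specific marker.
- **"Recording" can be read narrowly** as use of the same form. The sentence is then misleading and not strictly false. Closer questioning of people who are exercising is also legitimate.
- **The escalation rule is not the only safeguard.** Each AE is assessed for causality, repeated unexpected AEs prompt TMG review, and unexpected related SAEs go to the REC within 15 days. None of these needs a p-value.

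Three stronger readings are tempting, and the documents do not support them. A reader might infer that the plan will create an excess of events in the intervention arm. The direction is not fixed, because only controls have a named records check for AEs. A reader might take the 60- to 74-fold window as a difference in ascertainment. It concerns which SAEs are reviewed for attributability, and it depends on an ambiguous parenthesis. A reader might also infer that unequal ascertainment invalidates the escalation rule. Step 4 of the check shows that it does not at the stated complication rates.

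**Conclusion.** The point holds in two separate parts, plus one contradiction.

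1. AE and reportable-SAE counts by arm are not comparable as the protocol stands, despite the statement that recording is the same. The size depends on capture fractions that the protocol does not give. At half capture in one arm and true rates of 10–30%, a false significant difference would arise about 7–38% of the time, against 1.5% or less with equal capture. Admissions, 12-month SAE follow-up and MACE are largely unaffected.
2. The between-arm escalation rule needs at least 6 v 0 events and would miss a tripling of risk about 89% of the time at 3% v 9% and about 82% at 4% v 12%. This rests on a two-sided 5% Fisher test at one look with 53 per arm. It offers little protection, although individual causality review and TMG review remain.
3. Sections 9 and 13 contradict each other on whether expected exercise symptoms are AEs.

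The primary outcome is not touched. This is a should-fix.

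**What to change.** - **Common basis for comparison.** Restrict any between-arm AE or SAE comparison to events found from the same sources over the same window: the same questions at the CPET visits and next-day calls, and the same records check at 10 weeks and 12 months, extended to the intervention arm.
- **Separate listing.** Report events disclosed at exercise or education sessions as intervention-arm exercise safety data, outside the comparison.
- **Escalation wording.** Delete the statistical-significance condition from Assessment and Management of Risk, and have the TMG review complication counts by arm whatever the p-value.
- **Wording to reconcile.** State whether expected exercise symptoms are recorded as AEs so that sections 9 and 13 agree. State what the parenthesis on sessions in the reportable-SAE text is meant to limit. Bring the sentence on identical recording into line with the procedures that follow it.

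The cost is protocol wording plus a modest amount of records checking and data entry around existing visits. No new visits are needed, and the primary analysis and sample size do not change.

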# **MONITORING, AUDIT & INSPECTION**

The study may be monitored by the Research & Development Department at UHCW as representatives of the Sponsor, to ensure that the study is being conducted as per protocol, adhering to Research Governance and GCP. The approach to, and extent of, monitoring may be specified in a trial monitoring plan determined by the risk assessment undertaken prior to the start of the study.

# **ETHICAL AND REGULATORY CONSIDERATIONS**

- 1. **Ethical Approval and Research Governance**

The study will be conducted in compliance with the principles of the ICH GCP guidelines and in accordance with all applicable regulatory guidance, including, but not limited to, the UK policy framework for health and social care research. Ethical approval for this study will be sought from the Research Ethics Committee combined with Health Research Authority (HRA) approval. No study activities will commence until favourable ethical opinion and HRA approval has been obtained. Progress reports and a final report at the conclusion of the trial will be submitted to the approving REC within the timelines defined by the committee. Confirmation of capacity and capability will be obtained from the R&D department prior to commencement of the study at all participating sites.

- 1. **Notification of Serious Breaches to GCP and/or Trial Protocol**

A “serious breach” is a breach which is likely to effect, to a significant degree:

1. the safety or physical or mental integrity of the participants of the trial;
2. the scientific value of the trial

If a serious breach occurs, the sponsor will be notified immediately of any case where the above definition applies during the trial conduct phase.

- 1. **Peer Review**

Prior to submission to the research ethics committee, the study protocol and other patient facing documents have been reviewed by expert members in the field of cardiology and ablation.

- 1. **Public and Patient Involvement**

The study was presented to the Patient and Public Research Advisory Group (PPRAG) at UHCW to receive expert lay feedback on the study design and methodology. Following engagement with the PPRAG at UHCW they were supportive of this project. They recommended that people who do not have access to video conferencing software (smartphones or webcams) be excluded due to the reliance on the live exercise sessions at home in the CREED AF intervention. The group were also happy to see the familiarisation period incorporated into the programme.

- 1. **Data Protection and Patient Confidentiality**

The study will comply with the current Data Protection regulations and regular checks and monitoring will be undertaken by the Trial Manger to ensure compliance. Participants will be assigned a unique identifier upon enrolment into the study to allow pseudonymisation of patient-identifiable data. Access to patient identifiable data will be restricted to members of the study co-ordination team who require it for the performance of their role. Electronic data will be stored on password protected encrypted drives and hard copies of study documents will be stored in locked filing cabinets in secure entry-card protected sites.

# **DISSEMINATION POLICY**

Results of the trial will be prepared by the research team and lay partners and submitted to funders as a final report. Findings will be submitted to peer-reviewed journals and disseminated to the medical and exercise rehabilitation communities. Papers will be published in open-access journals describing the development of the CREED AF intervention, the trial protocol, and results and data, in accordance with recommended guidance for transparent reporting, the CONSORT guidelines (www.consort-statement.org) and UHCW SOPs: Publication & Dissemination. Abstracts will also be submitted to national and international conferences.

